**Methods:**

This is a single-center, randomized controlled trial, which includes a short-term VR intervention and a long-term real environment intervention. In the short-term intervention trial, 64 diabetic patients over 60 years old are randomly assigned to 1 of 7 intervention groups or a control group. All intervention groups are constructed by single or various combinations of the 3 indoor biophilic elements: natural decorative paintings, indoor potted plants, and ornamental fish. The primary outcome of the short-term intervention trial is the cognitive scores assessed by DSST and BDS. In the long-term intervention trial, 240 diabetic patients over 60 years old will be randomly assigned to either the intervention group or the control group. The biophilic elements in long-term intervention will be determined based on the results of the short-term VR intervention trial. The primary outcomes of the long-term intervention trial are cognitive scores measured by DSST and MoCA, as well as concentrations of plasma p-tau181, esRAGE, and IL-6.

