**Figure 1 fig1:**
[figure not shown]
Study flow chart. VR, virtual reality; A, natural decorative paintings; B, indoor potted plants; C, ornamental fish.

As for the short-term VR intervention trial, a total of 64 participants over 60 years old with diabetes are recruited. The participants are randomly assigned to seven intervention groups or a control group using block randomization with randomly selected block sizes. The main objective of the short-term trial is to determine which biophilic elements or their combinations show the most significant improvement in cognitive function.

As for the long-term real environment intervention trial, a total of 240 participants over 60 years old with diabetes will be recruited. The participants will be randomly assigned in a 1:1 ratio to either the intervention or control group. The main objectives of this long-term trial are to provide evidence for the healing effects of biophilic environments on cognition, and whether the *APOE4* genotype will modify the healing effects of biophilic environments on cognition in elderly diabetes.

Enrollment completion and final study visit are projected for December 2024 and December 2026, respectively.

This study was approved by the Ethics Committee of Capital Medical University (Approval No: Z2023SY019) and is conducted according to the ethical standards of the Helsinki Declaration. The study protocol was developed according to the Standard Protocol Items: Recommendations for Interventional Trials (SPIRIT) checklist.

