Preparation Phase: first, researchers provide a concise introduction to the study procedures. Participants rest for 5 min, and heart rate and blood pressure are measured using an Omron medical electronic blood pressure monitor (HBP-1300). Then, baseline data are collected through a questionnaire survey. The structured questionnaire includes general demographic characteristics such as age, gender, height, weight, ethnicity, education level, marital status, and income. It also includes lifestyle behaviors such as smoking, alcohol consumption, and physical activity, medical histories such as hypertension, diabetes, and cardiovascular disease, and medication history. An assessment of mental health status is conducted using the Center for Epidemiologic Studies Depression Scale (10-item, CESD-10). Finally, cognitive scores are assessed using the Digit Symbol Substitution Test (DSST) and the Backward Digit Span (BDS) scale. After the measurements, researchers provide the VR headset to participants and allow them to adapt and learn basic operations for up to 5 min. All VR devices look the same shape and color.Stress Phase: participants are exposed to a cluttered living environment through VR, with background noise from bustling traffic and mechanical devices. Then they undergo stress-inducing tests, including a memory test and an arithmetic test. The stress phase lasts for 5 min. After this phase, cognitive scores (DSST/BDS), heart rate, and blood pressure are re-measured.VR Intervention Phase: participants will engage in a 10–15 min of VR scenario intervention according to their group allocation. Depending on their groups, some participants may simulate activities such as walking indoors, opening doors, pulling curtains, watering plants, or feeding fish. After completing the VR intervention, cognitive scores (DSST and BDS), heart rate, and blood pressure are measured again. Additionally, the Environmental Semantics Differential Scale (SD) and the Restoration Scale (RS) are also evaluated.

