#### Short-term VR intervention trial

2.11.1

The randomized block analysis of the variance module of PASS 11.0 was used to calculate the sample size. According to previous literature (Liao et al., 2020), the MoCA scores would increase by 0.5 points, and the Chinese version of the Verbal Learning Test (CVVLT) immediate recall scores would increase by 1.0 point after VR intervention. The DSST has been found to be more sensitive than the MoCA and CVVLT. Thus, we conservatively assumed that the mean difference in DSST scores between the intervention and control groups would be 1.0, with a standard deviation of 1.2. The number of blocks was set at 8, the significance level was set at *p* < 0.05 and the statistical power was set at 90%. Based on the above parameters, the minimum sample size per block is six individuals. Considering the possibility of noncompliance or refusal to participate, the sample size was increased by 20%, resulting in eight individuals per block. Thus, there are eight blocks in the short-term trial, with each block containing eight individuals.

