#### Short-term VR intervention trial

2.12.1

The analysis will be carried out according to the intention-to-treat principle. Given the short duration of this trial, missing data is expected to be minimal. Therefore, a single imputation will be used to process the incomplete data. Outliers will be identified using the interquartile range (IQR) method, defined as values below Q1 − (1.5 × IQR) or above Q3 + (1.5 × IQR), and will be replaced with Q1 − (1.5 × IQR) and Q3 + (1.5 × IQR), respectively. One-way analysis of variance (ANOVA) (for continuous and normally distributed variables) and chi-square test (for categorical variables) will be conducted to assess the baseline equivalence between the eight groups. If there are differences in characteristics between groups at baseline, the differences will be adjusted by performing multiple linear regression. ANOVA will be used to compare whether there are statistically significant differences in cognitive scores, heart rate and blood pressure among the eight groups. For each group, paired *t*-tests will be conducted to examine whether changes in cognitive scores, heart rate, and blood pressure are statistically significant between baseline, pre-intervention, and post-intervention. The identification of optimal biophilic elements will follow a two-stage analytic protocol. First, multiple linear regression models adjusted for covariates will be fitted to compare post-VR intervention cognitive scores between each intervention group and the control. Groups achieving a covariate-adjusted *p* < 0.1 in these pairwise comparisons will be considered statistically promising. Subsequently, among these candidate groups, the intervention demonstrating the largest adjusted mean difference in cognitive scores relative to the control group will be selected for long-term real environment intervention. Multiple linear regression will be used to evaluate the cognitive improvement in each group after adjusting for covariates. Continuous variables will be assessed for normality prior to analysis. If the data are not normally distributed, the Kruskal-Wallis H test will be used to compare the differences between the eight groups.

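### Paired t-tests within each short-term arm cannot show that an element works; report within-arm change as description and base statements about elements on the contrast with control

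*Protocol article*

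**What the plan says.** Section 2.12.1 of the protocol article (short-term trial) plans paired t-tests within each group that "will be conducted to examine whether changes in cognitive scores, heart rate, and blood pressure are statistically significant between baseline, pre-intervention, and post-intervention". The cognitive scores are DSST and BDS, the primary outcome in Section 2.8.1. The paired tests are not labelled descriptive or exploratory, and Section 2.12.2 closes by applying a two-tailed 0.05 level to all tests in the study.

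Section 2.5.1 sets the sequence for every participant. DSST and BDS are taken at the start, and a 5-minute stress phase in a cluttered scene follows. Then: "After this phase, cognitive scores (DSST/BDS), heart rate, and blood pressure are re-measured". After 10 to 15 minutes in the assigned scene, the same measures are taken a third time. The Discussion (Section 3) grants that the VR device may itself affect cognition whatever scene is shown.

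Section 2.12.1 also plans an ANOVA across the eight groups and a two-stage selection. Post-VR scores in each intervention group are compared with control by covariate-adjusted regression. Groups with p < 0.1 become candidates, and the candidate with the largest adjusted difference from control goes forward. The main objective in Section 2.1 is worded differently: to "determine which biophilic elements or their combinations show the most significant improvement in cognitive function".

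**The concern.** A paired test within one arm asks whether that arm changed. It does not ask whether the arm changed more than control. Repeated testing, recovery after induced stress and wearing the headset act on all eight arms alike, and a paired test counts all of this as change in the arm concerned.

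Two patterns can then mislead. If the shared change is large, nearly every arm appears to improve. If it is moderate, arms of eight split by chance into significant and not significant, and an element arm can fall on one side with control on the other. That split looks like evidence for the element but says little about the difference between the two arms. An objective phrased as the most significant improvement makes this reading easier. At stake is what the short-term report says about single elements and combinations.

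**Working it through.** The plan states no power or error rate for the paired tests, so there is no figure of its own to reproduce on this point. (The sample size in Section 2.11.1 is a separate matter and is used here only for the arm size and the SD.)

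**Inputs from the protocol**
- Arms: "64 diabetic patients over 60 years old are randomly assigned to 1 of 7 intervention groups or a control group" (Abstract, Methods), so 8 arms.
- Arm size: 64 / 8 = 8. Section 2.11.1 words it as "there are eight blocks in the short-term trial, with each block containing eight individuals".
- Level: two-sided 0.05 (Section 2.12.2).
- DSST scale: "the mean difference in DSST scores between the intervention and control groups would be 1.0, with a standard deviation of 1.2" (Section 2.11.1), so SD 1.2.

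**Assumed, because the protocol does not give them**
- The shared true change, from 0 to 1.0 SD of the within-person change.
- The pre-post correlation, where the DSST scale is used.
- Normal changes, equal SDs, independent arms, and all eight people in each arm complete.

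**Step 1. Chance that one arm is significant in the improving direction.** For a standardized shared change d and n = 8, p = P(T > t), where t is the 0.975 quantile of the t distribution on 7 df and T is noncentral t on 7 df with noncentrality d × √8.

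**Step 2. Chance that control is not significant and at least one of the seven element arms is.** With no difference between arms this is (1 − p) × (1 − (1 − p)^7).

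| Shared change d (SD) | p per arm | Control not significant, at least one element arm significant |
|---|---|---|
| 0 | 0.025 | 16% |
| 0.25 | 0.089 | 44% |
| 0.5 | 0.231 | 65% |
| 0.75 | 0.448 | 54% |
| 1.0 | 0.681 | 32% |

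Example at 0.5: (1 − 0.231) × (1 − 0.769^7) = 0.769 × (1 − 0.159) = 0.647.

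The probability falls again at larger changes because control then tends to be significant too.

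**Step 3. The same on the DSST scale.** SD of the change = 1.2 × √(2 × (1 − correlation)). With an assumed correlation of 0.8 this is 1.2 × √0.4 = 0.76. A shared gain of 1.0 point is then d = 1.0 / 0.76 = 1.32, and p per arm is 0.89. About 8 × 0.89 = 7 of the eight arms would be significant although no element works. Over correlations from 0.5 to 0.9, p per arm runs from 17% to 62% for a shared gain of 0.5 point and from 53% to 99% for 1.0 point. With no shared gain it is 2.5%.

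**Step 4. The contrast with control on the same data.** In 20,000 simulated trials (shared gain 1.0, SD 1.2, correlation 0.8, no element effect), regression of the post score on arm and pre score gave p < 0.05 in 5.0% and p < 0.1 in 9.9% of arm-versus-control comparisons, which are the nominal rates. The shared gain cancels in the contrast but not in the paired test.

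**The case against.** The strongest reply is that nothing in the plan depends on these tests, and that stands. Section 2.12.1 selects the element only by regression against control, and the end of the Introduction gives a similar rule. No rule uses a paired-test result to choose an arm, to declare an element effective or to shape the long-term trial. A reader might infer that the paired tests decide which element goes forward, or that the conclusions about elements will rest on them. The document does not support either reading.

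A reader might also infer that practice and recovery are bound to make arms look improved. The protocol gives no size for such a gain. Over the assumed range, the chance of significance per arm runs from 2.5% to nearly 100%, so the text supports only that this can happen.

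A count of all paired tests would also exaggerate. The tests that bear on cognition across the intervention number 8 arms × 2 scales = 16. With no change at all, 16 × 0.05 = 0.8 would be significant, about half of them in the improving direction.

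Finally, not every paired comparison is misplaced. Whether the stress phase moved scores, heart rate or blood pressure is a within-person question, so deleting all the tests would lose a legitimate check.

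What remains is that the tests are planned on the primary outcome with no descriptive label. The Discussion argues that testing after both the cluttered and the clean scene may control for device effects. The before-after difference within an arm does not remove practice or recovery; the control arm does.

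**Conclusion.** The point holds as a minor one about interpretation and reporting of the short-term trial. A significant pre- to post-intervention change within an arm is not evidence for its element, because all arms share the test sequence. If all arms change equally, the misleading split between element arms and control occurs in about 16% to 65% of trials over shared changes of 0 to 1.0 SD, with the highest value in the table at 0.5 SD. These figures rest on eight completers per arm, normal changes with equal SD, independent arms, and a shared change whose size is assumed. The selection of the long-term intervention is not affected by the paired tests. However, the regression behind it does not explicitly secure adjustment for the pre-intervention score: Section 2.12.1 refers to covariates in general and to adjustment for characteristics that differ at baseline.

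**What to change.** - Report pre- to post-intervention change within each arm as a mean with a confidence interval, as description only and without a significance test.
- Keep the baseline to pre-intervention comparison, pooled over the eight arms, as a check of the stress phase.
- Base every statement about an element or combination on its contrast with control in the planned regression, with the pre-intervention score of the same measure always included as a covariate.
- Align the objective in Section 2.1 with the selection rule in Section 2.12.1, that is, the largest adjusted difference from control.

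The cost is a few sentences of analysis wording. The pre-intervention scores are already collected, and neither the sample size nor the visits change.

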#### Short-term VR intervention trial

2.5.1

The VR residential environment used in this study includes three elements: natural decorative paintings (A), indoor potted plants (B), and ornamental fish (C). Biophilic design encompasses three patterns: nature in the space, natural analogues, and nature of the space (Hung and Chun, 2021). Current research primarily focuses on the first two patterns and has found that biophilic elements such as plants (Verzwyvelt et al., 2021; Yin et al., 2020), animals (Motooka et al., 2006), and natural decorations (Shen et al., 2020) help alleviate stress and improve cognitive function. Considering the lifestyle habits of local older adults and the feasibility of practical implementation, our study employs the three biophilic elements. A blank control VR scene without biophilic design elements and seven biophilic design VR scenes (A, B, C, A + B, A + C, B + C, A + B + C) are employed. The experiment follows the subsequent steps. The trial flowchart is illustrated in Figure 2.

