Both the intervention and control groups will receive health behavior guidance, while the intervention group will additionally receive an indoor biophilic environment intervention. Health behavior guidance includes personalized health behavior and dietary guidance based on the Guideline for the prevention and treatment of type 2 diabetes mellitus in China (2020 edition) (Zhu and Society, 2021). Health promotion and personalized guidance will be conducted at each follow-up visit by medical doctors or professionals. The biophilic elements that are most effective in enhancing cognition during the short-term VR intervention trial will be used as the biophilic interventions in the long-term real environment intervention trial. Participants in the intervention group will be told to take the biophilic elements (such as indoor plants) home and place them in a visible place.

Long-term interventions will be followed up at 12 and 24 months. At the 12-month follow-up, behavioral risk factors, chronic disease history, Lubben scale for social interaction, PSQI, and DSST will be collected and a general physical examination will be performed. At the 24-month follow-up, behavioral risk factors, chronic disease history, Lubben scale for social interaction, PSQI, GDS-15, cognitive function (DSST, MoCA) will be assessed, a general physical examination will be performed, and blood samples will be collected again.

Blood samples will be collected in ethylenediaminetetraacetic acid (EDTA) anticoagulated vacutainer tubes. After centrifugation, blood cells and plasma will be stored separately. Plasma samples will be used for biomarker detection at both baseline and the 24-month follow-up, including glycated hemoglobin (HbA1c) levels, fasting blood glucose (FBG), tau phosphorylated at threonine 181 (p-tau181), endogenous secretory receptor for advanced glycation end-products (esRAGE), and interleukin-6 (IL-6). Blood cells will be used for DNA extraction and *APOE* genotyping. Blank control and duplicate samples will be used for quality control during the experiment.

At baseline and follow-up visits, we will fill out registration forms to record the use of the biophilic intervention facilities in the living room, in order to replace damaged biophilic elements in time and to provide persistent biophilic indoor environment intervention.

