#### Short-term VR intervention trial

2.8.1

Primary outcome: cognitive function, evaluated using the DSST and BDS scales.Secondary outcome: scores of the SD and the RS scales, as well as blood pressure and heart rate.

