#### Long-term real environment intervention trial

2.12.2

The modified intention-to-treat population (mITT) will be used for statistical analysis. Missing values will be imputed using multiple imputation. Firstly, two sample t-tests (for continuous and normally distributed variables) and chi-square test (for categorical variables) will be conducted to assess the baseline equivalence between the intervention and control groups. Two sample t-tests will be used to compare whether cognitive scores are statistically different between two groups. Multiple linear regression will be used to demonstrate whether the intervention is statistically associated with cognitive scores after adjusting for potential confounders. Repeated measures ANOVA will be used to compare cognitive scores across groups. The potential confounders will be corrected in the mixed-effect model to determine the association between intervention and cognitive scores. If the intervention has a direct effect on cognitive function, longitudinal causal mediation analysis will be further used to clarify the mediating factors through which the intervention may affect cognition.

To explore the interaction of *APOE4* and the biophilic environment on cognition, we will perform stratified analysis according to groups to clarify the main effects of *APOE4* on cognitive function. Then, mixed models will be used to adjust for potential covariates and to elucidate the main effect of *APOE4* on cognitive function in each group. Finally, the interaction term between the *APOE4* and the intervention group will be included in the mixed-effects model to identify the effect of the genetic-environmental interaction on cognitive function.

In our study, all statistical tests are two-tailed, with a significance level of *p* < 0.05.

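### The unadjusted p<0.1 screen of seven VR scenes against one shared control labels some scene promising in about 40% of null trials on a single test (about 20% counting benefit only)

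*Protocol article*

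**What the plan says.** All references are to the protocol article.

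- Section 2.5.1 sets up the arms: "A blank control VR scene without biophilic design elements and seven biophilic design VR scenes". Section 2.11.1 gives 64 people in total, which is eight per arm.
- Section 2.8.1 names two tests without ranking them: "Primary outcome: cognitive function, evaluated using the DSST and BDS scales".
- Section 2.12.1 fits covariate-adjusted regressions "to compare post-VR intervention cognitive scores between each intervention group and the control". The rule is then that groups with a covariate-adjusted p<0.1 "in these pairwise comparisons will be considered statistically promising". Among those groups, the one with the largest adjusted mean difference goes into the long-term trial. The Introduction gives the same rule (largest effect size together with p<0.1).
- The overall ANOVA in section 2.12.1 is a separate comparison and not a gate for this step. No direction is set for the p<0.1 step, and there is no statement of whether a scene must pass on DSST, on BDS, on either or on both.
- Section 2.1 makes it the main objective of the short-term trial to "determine which biophilic elements or their combinations show the most significant improvement in cognitive function". Section 2.5.2 carries the result over in firm language: "The biophilic elements that are most effective in enhancing cognition during the short-term VR intervention trial will be used".
- Section 2.12.2 closes with a statement for the study as a whole that "all statistical tests are two-tailed, with a significance level of" p<0.05, which does not match the 0.1 used in section 2.12.1.

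**The concern.** The word covariate-adjusted describes the regression model; it does nothing about the number of comparisons. A 10% level describes one comparison, but the rule looks at seven and keeps the best of those that pass. Its chance of labelling something promising when nothing works is therefore well above 10%. The selected difference is also biased upwards, because it must first clear a threshold and then be the largest.

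This matters because the short-term trial's main objective is answered by this rule, and section 2.5.2 words the result as a finding of effectiveness. At stake are an overstated conclusion from the short-term trial and the possibility that 240 people are followed for 24 months on a scene picked by chance.

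**Working it through.** **Plan's own figure.** The protocol states no error rate for the screen, so there is none to reproduce.

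**Inputs.** Seven scenes and one control (section 2.5.1); eight per arm (section 2.11.1); two-sided p<0.1 per comparison (sections 2.12.1 and 2.12.2); DSST difference 1.0 with SD 1.2 (section 2.11.1). Residual degrees of freedom: 64 − 8 = 56 before covariates. The DSST-BDS correlation is not in the document; it is an assumption, varied from 0 to 0.9.

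**Step 1: what a scene needs to pass.** The test statistic is t = (scene mean − control mean) / (s·√(2/8)). The two-sided 10% point on 56 df is 1.673. The smallest passing difference is therefore 1.673 × √(2/8) = 0.836 SD, or 0.836 × 1.2 = 1.00 DSST point when the sample SD equals 1.2. A scene can pass only if its observed benefit is about as large as the whole effect assumed in the plan.

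**Step 2: false labels when no scene works.** Treating the seven comparisons as independent would give 1 − 0.9^7 = 52%. They share a control group, so they are correlated 0.5 and the true figure is lower. Simulated null trials (8 arms of 8, pooled variance) give the chance of at least one scene with p<0.1:

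| Reading of the rule | Any direction | Better than control only |
|---|---|---|
| One test | 40% | 20% |
| Either test, correlation 0 | 64% | 36% |
| Either test, correlation 0.5 | 61% | 32% |
| Either test, correlation 0.7 | 57% | 30% |
| Both tests required, correlation 0 to 0.9 | 6% to 28% | 1.5% to 14% |

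Separate two-group t-tests in place of the pooled model give 40% on one test and 64% and 62% on either test (correlation 0 and 0.5). Six per arm instead of eight hardly changes anything.

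**Step 3: size of a falsely declared benefit.** In the null trials where a scene passes on DSST in the beneficial direction, the best scene's mean observed advantage is about 1.05 SD: 1.05 × 1.2 = 1.26, about 1.3 points.

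**Step 4: thresholds that hold 10%.** Two-sided Dunnett for seven comparisons on 56 df: |t| > 2.40, unadjusted p < 0.020, for one test. Splitting the 10% as 5% to each test: |t| > 2.69, unadjusted p < 0.009 each.

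**Step 5: what each rule does when one scene works.** Take one scene with a true difference of 1.0 at SD 1.2 and six with none. The noncentrality is 1.0 / (1.2 × 0.5) = 1.67.

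- The effective scene passes p<0.1 in 50% of trials, and the Dunnett threshold in 24%.
- It is selected (passes p<0.1 in the right direction and is the largest) in about 47% of trials.
- By ranking alone, with no p-value gate, it is selected in about 82%.

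The 50% is the power of one scene-versus-control comparison. It is not the 90% of section 2.11.1, whose derivation is not examined here.

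**The case against.** The strongest defence is that this is a screen. The protocol applies p<0.1 to each pairwise comparison, uses a hedged label, and calls the VR results a reference for a separately randomised trial of 240 people. That trial's type I error is not inflated, and its sample size is built on vegetation-index data, not on the VR estimate. A lenient per-comparison level is a defensible choice before independent testing, and a Dunnett gate would halve the chance of passing an effective scene. All of this stands. It rules out a Dunnett threshold as the selection rule. It does not justify the wording in sections 2.1 and 2.5.2, which goes beyond screening.

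A reader might infer that the plan produces a false optimal element about 60% of the time, or more often than not. The document does not support that. The 57-64% needs a pass on either test to count, which is stated nowhere, and it includes scenes that did worse than control. Sections 2.1 and 2.5.2 speak of improving and enhancing cognition, so only beneficial scenes would plausibly be chosen: about 20% on one test and 30-36% on either.

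It may also be tempting to blame the shared control for a wrong choice of scene. A low control mean raises all seven differences equally. It can make several pass together, but it cannot change their order, and sharing lowers the overall rate (40% against 52%).

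How two endpoints combine can be left to an analysis plan that is not shown. The gap is raised here only because the error rate of the rule as printed depends on it.

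**Conclusion.** The point holds as a matter of what the short-term trial may claim. On a single test, the rule labels at least one scene promising in about 40% of trials with no effect, four times the level of one comparison; counting benefit only, it is about 20%. Under an either-test reading these become 57-64% and 30-36% for assumed correlations of 0.7 to 0; if both tests were required, they would be much lower. A falsely declared DSST benefit averages about 1.3 points against an assumed true effect of 1.0. The figures assume normal scores, equal variances, eight completers per arm and 56 residual df; covariates would reduce the df slightly. The consequence is an overstated conclusion and a scene possibly chosen by chance, not a flawed test in the long-term trial. It should be changed, but it does not undermine the design.

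**What to change.** In section 2.12.1, with matching wording in the Introduction and sections 2.1 and 2.5.2:

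1. Choose the scene for the long-term trial by the largest adjusted mean benefit over control, and state that it was selected by ranking and not shown to be effective.
2. Reserve the terms promising and most effective for scenes with two-sided Dunnett-adjusted p<0.1 in the beneficial direction (about unadjusted p<0.020 on one test), and report Dunnett simultaneous intervals.
3. State whether DSST or BDS drives the ranking. If both carry the claim, split the 10% between them (about unadjusted p<0.009 each).
4. Reconcile the 0.1 level with the blanket p<0.05 in section 2.12.2.

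Do not make the Dunnett threshold the gate for selection: the chance that one effective scene passes would fall from about 50% to 24%.

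The cost is a few sentences and no extra participants. A scene will be labelled promising less often. Ranking always carries some scene forward, even when none works, which is why the wording in item 1 is needed. In return, under the plan's own assumptions, a single effective scene is picked in about 82% of trials instead of 47%.
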